## Abstract

**Background:**

Rheumatoid arthritis (RA) is a condition with symptoms that vary over time. The typical 3- to 6-month interval between physician visits may lead to patients failing to recall or underreporting symptoms experienced during the interim. Wearable digital technology enables the regular passive collection of patients’ biometric and activity data. If it is shown to be strongly related to data captured by patient-reported outcome (PRO) measures, information collected passively from wearable digital technology could serve as an objective proxy or be complementary to patients’ subjective experience of RA symptoms.

**Objective:**

The goal of this study is to characterize the extent to which digital measures collected from a consumer-grade smartwatch agree with measures of RA disease activity and other PROs collected via a smartphone app.

**Methods:**

This observational study will last 6 months for each participant. We aim to recruit 250 members of the ArthritisPower registry with an RA diagnosis who will receive a smartwatch to wear for the period of the study. From the ArthritisPower mobile app on their own smartphone device, participants will be prompted to answer daily and weekly electronic PRO (ePRO) measures for the first 3 months.

**Results:**

The study was launched in December 2018 and will require up to 18 months to complete. Study results are expected to be published by the end of 2021.

**Conclusions:**

The completion of this study will provide important data regarding the following: (1) the relationship between passively collected digital measures related to activity, heart rate, and sleep collected from a smartwatch with ePROs related to pain, fatigue, physical function, and RA flare entered via smartphone app; (2) determine predictors of adherence with smartwatch and smartphone app technology; and (3) assess the effect of study-specific reminders on adherence with the smartwatch.

**International Registered Report Identifier (IRRID):**

DERR1-10.2196/14665

## Introduction

As the selection and availability of consumer-grade digital technology to measure biometric and activity outcomes have increased dramatically in recent years, their use in clinical and observational studies have also grown. At a minimum, biosensor technology typically measures heartbeat, activity, and sleep, yet these tools have been used primarily in research in disease states with core symptoms that are clearly directly measurable using such technology (eg, Parkinson’s disease) [1]. An individual’s level of activity and sleep quality can be affected by many other conditions, such as migraine, diabetes, systemic lupus erythematosus, atopic dermatitis, obesity, and arthritis. The ability to observe symptom changes in real time (particularly in response to pharmacotherapy and behavior changes) using mobile biosensor technology has the potential to significantly enhance treatment of chronic disease by enabling more rapid and focused deployment of interventions.

Rheumatoid arthritis (RA) is the most common autoimmune inflammatory arthritis and often results in joint damage that, without adequate treatment over time, may lead to disability, pain, limitations in physical function, and other impairments important to patients [2]. Treating clinicians typically see RA patients at 3- to 6-month intervals. Assessments at clinician visits are necessary, but not enough, to understand the full spectrum of a patient’s clinical state, progression, and the waxing and waning nature of their symptoms. The true severity of pain and flares experienced between visits may not be captured at office visits due to recall bias. To understand the extent of RA disease activity, especially attributes related to pain and stiffness, it is essential to collect patient-reported outcome (PRO) measures in a low-burden, continuous frequency instead of an episodic frequency. PRO measures may include health-related quality of life, physical function, fatigue, sleep, mental health status, work productivity and work activity impairment [3].

PRO measures direct patients to report on their experience and therefore supply unique data for the management of RA. Because PROs are reported directly by patients on paper or electronic questionnaires, they reflect how a patient feels and functions in relation to RA and its therapy [4,5]. Although PRO measures necessitate patient attention and effort, they are also useful for understanding a patient’s subjective experiences. They can help to facilitate clinician-patient communication and shared decision-making to improve the quality of patients’ care, and they can help to identify both common and divergent perceptions of disease activity and treatment effectiveness between clinician and patient. While the advent of smartphone technology has enabled convenient and remote capturing of electronic PRO measures (ePROs) between in-person clinician visits [6,7], a patient must still recall their symptoms over a day- or week-long period. In the quest for additional patient-generated data to complement patients’ reported experiences of physical function, pain, sleep, fatigue, and so on, biometric sensors may play an important role in providing continuously captured objective data (ie, activity, heart rate and sleep hours).

To date, there are few published studies investigating the extent to which biometric data correspond with RA patients’ subjective reports of their symptoms and disease activity. Performance outcome measures (eg, gait, distance traveled, and acceleration) collected passively using smartphone applications have been found to be associated with RA symptoms in studies with small samples ranging from 20-80 participants [8,9]. A recent proof of concept, human factors study explored the experience of 15 subjects who wore an activity tracker daily over 1 week and completed ePRO questions about stiffness, sleep quality, and joint pain in the morning and evening. The investigators reported that initial analyses showed modest correlation between the duration of morning stiffness reported in the ePRO and the level of morning activity tracked by the activity tracker. These investigators are planning a larger trial in a clinical setting with RA subjects receiving medication [10].

In a study of 446 participants, of whom 292 were RA patients, data from daily passive digital measures (ie, Global Positioning System–tracked mobility, mobility radius number, and duration of calls and texts) were collected and associated with PRO measure data (ie, daily pain, patient global health assessment, weekly Health Assessment Questionnaire-II [HAQ-II] [11] and Patient Activity Scale-II [PAS-II] [12]). Text length was most strongly and inversely associated with PROs, including pain, and mobility measures were significantly associated with global assessment, HAQ-II, and PAS-II, but not pain [13]. The Patient Rheumatoid Arthritis Data from the Real World (PARADE) study, launched in 2016, collected ePROs and both active and passive digital data through a smartphone-customized ResearchKit application to measure morning stiffness and fatigue [14,15], but it had disappointing levels of patient engagement. Specifically, of 399 recruited participants, less than half (162; 40.6%) completed one or more study assessments at week 2, and only 45 (11%) remained active in the study by 12 weeks [15,16].

Our exploratory study will expand on these prior studies and examine a larger RA population, incorporating digital measures from a Fitbit Versa smartwatch (chosen based on the type of biometric data captured, water resistance and cost) to assess the value of passively collected digital measures as proxies for RA disease activity and other domains of health that may be affected by RA, as reflected in ePROs. Our study differs from PARADE in the use of smartwatch technology and in the manner of participant recruitment. The PARADE study developed a set of wrist activities to measure range of motion [15], but the activity measurement in our study will be passively collected with the smartwatch. Although less sensitive measures are available via the smartwatch, the ability to collect some measure of activity without requiring participant input is an advantage. In addition, PARADE used a broader approach to identify participants in the United States via targeted digital marketing on social media platforms including Facebook, Twitter, and HealthUnlocked. They also made study information available to Facebook users who followed CreakyJoints. In contrast, our study will enroll patients exclusively from members of ArthritisPower, a CreakyJoints-affiliated research registry in the United States. We believe working within an existing population that is already oriented to sharing ePROs will result in greater participant retention. Unlike PARADE, there will be no randomization into groups based on data sharing with the participant during our study, as all participants will be able to view the same amount of their own data throughout. Additionally, PARADE was conducted entirely via app, with no financial incentives and human interaction. In our study, participants will receive compensation based on specific milestones, and members of the research team will monitor their data in real time and, under certain criteria, contact participants when missing data patterns suggest nonadherence to protocol or difficulty in using the technology. Real-time data monitoring offers the opportunity to clarify protocol procedures directly with individual participants.

Specifically, this study seeks to evaluate the potential relationship between passively collected digital measures related to activity, heart rate, and sleep, collected from a smartwatch, with ePROs related to pain, fatigue, physical function, RA disease activity and flare in participants with RA over the 3-month main study period. In the lead-out period, participants’ use of smartwatch technology will continue to be observed for another 3 months.

The secondary objectives of this study are to: (1) examine the variability of measurement of data derived from digital measures; (2) assess the test-retest reliability and both the convergent and discriminant validity of the digital measures; and (3) determine predictors of adherence with the technology, both with the app and smartwatch.

Exploratory objectives of this study include: (1) evaluating the effect of reminders on adherence with smartwatch use by comparing engagement during the main study period (months 1-3) and lead-out period (months 4-6); and (2) identifying the scientific and operational benefits as well as the challenges confronted in characterizing the burden of illness in RA with digital measures to inform future, digital, real-world evidence studies.

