#### Main Study Period

Upon successful completion of the lead-in period, participants will receive a Participant Kit that will contain a smartwatch, on-boarding and training materials, and instructions to access study resources such as frequently asked questions, training videos, and research team contact information. Participants will receive reminders as smartphone lock-screen notifications and as emails to sync their smartwatch data and complete their ePROs during the subsequent 84 days. To avoid sending extraneous notifications to those participants who are consistent in smartwatch data download, syncing, and ePRO completion, ArthritisPower will use the daily Fitbit and ePRO data to provide targeted text, email, and phone follow-up reminders, as well as support to participants whose data are missing for one or more days.

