#### Lead-Out Period

Following the main study period is a three-month lead-out period, during which no reminders to sync the smartwatch will be sent and no ePRO collection will be prompted beyond normal monthly reminder emails that are sent to all participants in the ArthritisPower registry. The purpose of the lead-out period is to assess the effect of reminders on the main study, observe the attrition in smartwatch use, and assess any changes in smartwatch measures when not actively solicited.

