### Compensation

Participants who complete all activities for the first 4 weeks of the main study period will receive a US $25 gift card, and those who complete all activities for all 12 weeks of the main study period will receive an additional US $50 gift card.

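### Comparing months 1-3 with months 4-6 in one cohort cannot isolate the effect of reminders on smartwatch adherence, because elapsed time, ePRO prompting, the last gift card and the minimum tracker commitment also differ between the periods

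*Protocol article*

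**What the plan says.** The Introduction gives as the first exploratory objective "evaluating the effect of reminders on adherence with smartwatch use by comparing engagement during the main study period (months 1-3) and lead-out period" (months 4-6). The abstract's Conclusions promise that the completed study will "assess the effect of study-specific reminders on adherence with the smartwatch". The Lead-Out Period section repeats the aim and gives the same period a second use: "The purpose of the lead-out period is to assess the effect of reminders on the main study, observe the attrition in smartwatch use".

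The design is a single cohort: "This observational study will last 6 months for each participant". No group with a different reminder schedule is described.

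Four other sections bear on what else differs between the periods:

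- **Lead-Out Period:** "no reminders to sync the smartwatch will be sent and no ePRO collection will be prompted beyond normal monthly reminder emails", the exception being the emails that all registry members receive.
- **Compensation:** a US $25 card is earned for the first 4 weeks, and "those who complete all activities for all 12 weeks of the main study period will receive an additional US $50 gift card". No payment is stated for the lead-out.
- **Main Study Period:** missing data trigger "targeted text, email, and phone follow-up reminders, as well as support to participants whose data are missing for one or more days". This is described under that period only.
- **Textbox 1 (inclusion criteria):** participants must be willing to give tracker data for a minimum of 84 days, which is the length of the main period.

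The article names no estimator for the comparison and does not list its interpretation as a limitation.

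**The concern.** The objective asks a causal question about one component, reminders, and fixes the contrast that is to answer it. That contrast is an uncontrolled before/after comparison in which several possible drivers of watch use move together. The protocol itself treats these as drivers. The Introduction offers compensation and staff contact as differences from an earlier app-based RA study with poor retention, and the Lead-Out Period section expects attrition.

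If the comparison is reported as planned, attrition and the end of incentives and tasks would be credited to reminders. The second exploratory objective is to inform future digital studies, so a reader may use the result to decide whether to pay for a reminder system. The choice of contrast is written into the objective, so this is not a detail left to an analysis plan.

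**Working it through.** **Stated figure.** There is none for this objective. The article's only power statement concerns the primary correlations and has no bearing here.

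**Step 1: what differs between the periods, and how firmly the article says so.**

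| Factor | Status in the article |
|---|---|
| Sync reminders | Stop at lead-out: stated |
| ePRO prompting | Stops at lead-out: stated, but the Figure 1 legend conflicts |
| US $50 milestone | Reached at week 12, none after: stated |
| Minimum tracker commitment | 84 days: stated |
| Attrition over time | Expected and observed in the same lead-out period; gradual, with no step at day 84 |
| Targeted support, case management | Support described for the main period only; no end date given |

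The legend of Figure 1 says the two daily questionnaires carry on through the whole study. The abstract's Methods limit prompting to the first 3 months, and the Lead-Out Period section stops it. Textbox 1 asks for ePROs for up to 98 days, which equals the 14-day lead-in plus the 84-day main period (14 + 84 = 98) and so agrees with the latter two.

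**Step 2: how large a difference can arise with no reminder effect.** The inputs below are assumptions, since the article gives no wear rates for this cohort. Let the proportion of days worn in week k (k = 0 to 23) be

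p(k) = 0.95 - w·k - s·[k ≥ 12],

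where w is the weekly decline and s is the total step at week 12, made up of a reminder part and a non-reminder part.

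- Mean of weeks 0-11: 0.95 - 5.5w
- Mean of weeks 12-23: 0.95 - 17.5w - s
- Difference: 12w + s (the 0.95 starting level cancels)

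With s = 0, so that nothing at all happens at week 12:

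| Decline per week | Months 1-3 | Months 4-6 | Difference |
|---|---|---|---|
| 0.5 points | 92.25% | 86.25% | 6 points |
| 1.0 point | 89.5% | 77.5% | 12 points |
| 2.0 points | 84.0% | 60.0% | 24 points |

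With no decline and no reminder effect, a drop of 5 or 10 points from ending prompts and incentives gives a difference of 5 or 10 points.

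**Step 3: what modelling the trend can and cannot recover.** Take a decline of 1 point per week and two different truths:

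- Reminder effect 5, other withdrawals 5: difference 12 + 10 = 22 points; step net of trend 10 points.
- Reminder effect 0, other withdrawals 10: difference 12 + 10 = 22 points; step net of trend 10 points.

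A segmented model removes the 12 points due to smooth decline. The remaining 10 points are the same under both truths, so no analysis of these data can split them.

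**The case against.** **Exploratory aim.** The study calls itself observational and exploratory, and its correlation analyses and sample size do not depend on this objective. That is right, and it limits the severity.

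**The estimator is not stated.** The article says only that engagement will be compared, and an analysis plan that is not shown may model the time course. Table 1 also defines persistence, which concerns timing. It would therefore be wrong to say that the study plans a contrast of period means. This answers the trend part of the problem at most: Step 3 shows that simultaneous withdrawals remain inseparable under any model.

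**Some changes are part of the exposure.** Reminders in the main period cover both syncing and ePROs, and the targeted follow-up messages are themselves called reminders. On a broad reading of study-specific reminders, these belong to the exposure. That is fair. The objective, however, does not define the exposure that way, and elapsed time, the US $50 milestone, the 84-day commitment and the ePRO task itself remain outside it.

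**Stronger readings that the article does not support.**

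- A reader might infer that every engagement factor ends at day 84. Attrition is gradual, the US $25 card is earned at week 4, and the end of case management is nowhere stated.
- A reader might object that targeted reminders go to people already missing data, which confounds comparisons within months 1-3. No such comparison is planned.
- A reader might conclude that the study is bound to report a false effect of a given size. That needs an actual decline or withdrawal effect, and the article gives no rate from which to compute one.

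**Conclusion.** The concern holds in limited form. A same-order, single-cohort comparison of months 1-3 with months 4-6 cannot isolate a reminder effect, because attrition and at least three other documented changes (ePRO prompting, the US $50 milestone and the minimum tracker commitment) fall on the same side of the comparison. The documented end of ePRO prompting is subject to the Figure 1 conflict; the conclusion does not depend on it.

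The 6 to 24 points are an illustration under an assumed linear decline of 0.5 to 2 points per week and no reminder effect. They show that a nonzero difference is not evidence of a reminder effect; they do not predict its size in this study.

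This should be fixed, but it does not threaten the study. The objective is exploratory, and what is at risk is a conclusion that the abstract promises.

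**What to change.** 1. **Analysis.** Analyse daily wear with a segmented (interrupted time-series) model: a participant random effect, a slope before day 84, and a level change and a slope change at day 84. Smooth decline is then not counted as an effect. The result still depends on the assumed form of the earlier trend.
2. **Objective and abstract.** Restate both as the change in smartwatch adherence after the whole study engagement package ends (reminders, ePRO prompts, follow-up support and incentives). Drop the causal claim about reminders alone.
3. **Limitation.** State that components withdrawn together cannot be separated and that there is no concurrent control. Say when targeted support and case management end.
4. **Consistency.** Reconcile the Figure 1 legend with the abstract's Methods and the Lead-Out Period section on whether daily questionnaires continue, since this decides whether ePRO activity changes at day 84.

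The cost is one additional model on data already being collected, some rewording, and a more modest conclusion. No new data collection or design change is needed.

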## Methods

### Research Design

#### Overview

This is an ancillary study conducted within the ArthritisPower registry infrastructure. ArthritisPower was jointly developed by the nonprofit Global Healthy Living Foundation (GHLF), its associated CreakyJoints arthritis patient community, and rheumatology researchers at the University of Alabama at Birmingham (UAB) [17,18], and funded through a Patient-Centered Outcomes Research Institute Award (Contract Number PPRN-1306-04811). ArthritisPower currently has over 18,000 consenting participants, about half of whom report a physician diagnosis of RA. As part of their membership in the ArthritisPower registry, participants have downloaded the ArthritisPower app used for ePRO measures collection. This ancillary study, sponsored by Eli Lilly and Company, will collect ePRO measures from RA participants via a customized, study-specific user flow within the ArthritisPower app while measures of activity, heart rate, and sleep will be collected passively using the smartwatch.

The DIGITAL Tracking of rheumatoid Arthritis Longitudinally (DIGITAL) study includes a 10- to 14-day lead-in period, 12-week main study period, and 12-week lead-out period (Figure 1).

#### Lead-In Period

Prior to receiving their smartwatch, invited participants will successfully complete a 14-day lead-in period during which they are required to meet the following inclusion criteria: (1) complete two daily ePRO measures, specifically the single-item Pain and Fatigue numeric rating scales (NRS), on at least 10 of the 14 days; and (2) complete two weekly core sets of ePRO measures (Table 1), over the 14-day period. Those who do not meet these requirements will be offered a single opportunity to repeat the lead-in period and subsequently qualify for the remainder of the DIGITAL study. This initial phase will serve to acclimate participants to regular data collection and provide some assurance that they are willing and able to take part in and complete study requirements over the 3-month main study period.

**Figure figure1:**
[figure not shown]
Overall study design. *Active data collection of 2 daily questionnaires begins 2-4 weeks prior to receipt of smartwatch and continues throughout the study. Other electronic patient-reported outcomes measures will be collected weekly. Digital data from the smartwatch will be collected passively.

**Table 1 table1:** Variables and measures.

Categories and variables (frequency/source)			Definition
